#### **Diabetic Retinopathy:**

DR will be graded using the standard classification (from reference [8])

#### **DIABETIC RETINOPATHY DISEASE SEVERITY SCALE**

| Disease Severity Level | Findings Observable upon Dilated Ophthalmoscopy                                                                                                                                                                                                     |
|-------------------------------|------------------------------------------------------------------------------------------------------------------------------------------------------------------------------------------------------------------------------------------------------------|
| No apparent retinopathy       | No abnormalities                                                                                                                                                                                                                                           |
| Mild NPDR                     | Microaneurysms only                                                                                                                                                                                                                                        |
| Moderate NPDR                 | More than just microaneurysms but less than severe NPDR                                                                                                                                                                                                    |
| Severe NPDR                   | Any of the following (4-2-1 rule) and no signs of proliferative retinopathy:
Severe intraretinal hemorrhages and microaneurysms in each of four quadrants
Definite venous beading in two or more quadrants
Moderate IRMA in one or more quadrants |
| PDR                           | One or both of the following:
Neovascularization
Vitreous/preretinal hemorrhage                                                                                                                                                                      |

IRMA = intraretinal microvascular abnormalities; NPDR = nonproliferative diabetic retinopathy;

PDR = proliferative diabetic retinopathy

**Data collection:** A database will be designed to capture:

1. Basic details from the eligible patients such as name, age, contact information, blood sugar level, HBA1C, duration of diabetes, date of diagnoses, other vascular complications etc.
2. Details of the fundus examination also will be recorded for participants from both the arms
3. Responses to interview that probe barriers to non-response and drivers of acceptance

**Sample size estimates:**

The following preliminary assumptions were made:

- (i) The proportion of patients in UR diagnosed with DR at AEH is 30% of the referred patients
- (ii) The proportion of patients in TR diagnosed with DR at AEH is 50% of the referred patients
- (iii) Power of 90% and alpha of 0.01 for a 2 sided test
- (iv) The design effect is 2 (derived from reference [4])

The estimated total sample size is 616 patients, equally distributed in each arm. Each of the 8 centres will recruit between 80 and 100 patients eligible for referral to AEH. We anticipate the time taken to recruit this number of eligible patients will be approximately 6 months. This is a conservative estimate because it is likely that a substantial number of eligible patients will be available. Population estimates show that the proportion with DR in diabetics is 12% and is higher in urban areas, in high income groups and in older people (50+) and with longer duration of diabetes [5].

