### Rationale

Diabetes Mellitus (DM) is a major health problem estimated to have affected 171 million people worldwide in 2000 and projected to rise to 366 million in 2030 [1]. India has the highest number of people with diabetes in the world with 31.7 million in 2000. This figure is estimated to rise to 79.4 million by 2030, based only on demographic changes, i.e. the growth of the older population where diabetes is more prevalent. However, lifestyle changes, especially increasing levels of obesity may lead to an even greater number of people with DM in India. Consequences of DM include Diabetic Retinopathy (DR) which is a major cause of avoidable blindness in both developing and the developed countries [2] and patients with DR are 25 times more likely to become blind than non-diabetics. Various studies conducted in India shows that 12 – 18% of the diabetic population develops DR [3-6]. In a population-based study conducted by Aravind Eye Hospitals in the Theni district of south India the prevalence of DM was found in 10.8 % of people aged 30 and over; of whom 12.2% had DR [4]. Prevalence rates of both DM and DR were higher in older people and in urban compared to rural areas.

Timely treatment can prevent vision loss due to diabetic retinopathy [7]. Treatment can yield substantial cost savings compared with the direct costs for those disabled by vision loss [8]. Though all diabetics require regular monitoring for diabetic retinopathy, only a very small proportion of the “known diabetics” receive a comprehensive eye examination [8]. Factors such as lack of access to eye hospitals, lack of ophthalmologists trained in diabetic retinopathy management and lack of awareness both by diabetic physicians, optometrists and patients. In particular, lack of knowledge among physicians and optometrists regarding diabetic retinopathy is highly unacceptable [9]. A study conducted on the awareness level of physicians in India reported that more than 67% of the physicians were unaware and about 10% were only partially aware of diabetic retinopathy [10]. When patients do attend ophthalmology clinics, it may be at a late stage of disease and their prognosis is poor. Treatment of end stage DR does not provide satisfactory results and is frustrating for both the patient and the ophthalmologist [3].

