Population screening for diabetes and DR is costly and therefore is not appropriate as a regular screening strategy to identify DR. In the exiting context of healthcare, the critical challenges that need to be addressed include:

- a. Identifying diabetics at risk of DR through targeted screening of known diabetic patients at diabetic/physician centres
- b. Ensuring easy access to an ophthalmic centre for the diabetic patients who require further intervention
- c. Enabling patients diagnosed with DR to comply with regular follow-up either at diabetic/physician centres or the ophthalmic centres, as appropriate

The conventional system is to refer all patients identified with diabetes to undergo an eye examination at an ophthalmic centre. However, only a very small percentage of the people referred in this mode actually present at the ophthalmic centre for an eye examination to confirm or rule out the presence of DR [11,12]. Thus opportunities for intervention and management of DR are lost.

Fundus examination is adequate for diagnosing DR and its severity. Technological advances in ophthalmic care have enabled the availability of digital imaging of fundus making it easier and more widely accessible [13]. Digital retinal photography without mydriasis by trained office staff has been reported as an effective mechanism to examine patients who are in need of diabetic retinopathy screening [14]. Use of telemedicine has been, in many instances, found to be valid and effective in achieving better outcome in the screening of, and interventions for, diabetes related complications as well as other systemic diseases [15-18]. Implementing retinal imaging technology in a primary care setting has been found to have resulted in a significant increase in rate of DR surveillance and in the rate of laser treatment for DR [11, 19]. But, there has not been an RCT to evaluate robustly the effectiveness of telemedicine in case finding of DR.

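### The 30% DR rate assumed for universal referral conflicts with the protocol's own prevalence and attendance statements, so the 90% power claim is not tied to rates the protocol supports

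*Protocol*

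**What the plan says.** Under Sample size estimates the protocol lists preliminary assumptions, none of the rates with a source: "The proportion of patients in UR diagnosed with DR at AEH is 30% of the referred patients"; "The proportion of patients in TR diagnosed with DR at AEH is 50% of the referred patients"; "Power of 90% and alpha of 0.01 for a 2 sided test"; and a design effect of 2. It concludes: "The estimated total sample size is 616 patients, equally distributed in each arm". Each of the 8 centres is to recruit 80-100 patients eligible for referral, or 640-800 in all.

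The same section says "Population estimates show that the proportion with DR in diabetics is 12" per cent. It adds, without a figure, that DR is commoner in urban areas, in high income groups, in people aged 50+ and with longer diabetes. The Rationale gives "12 – 18% of the diabetic population develops DR" for Indian studies and 12.2% for one district. Of conventional referral it says that "only a very small percentage of the people referred in this mode actually present at the ophthalmic centre".

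Under Outcomes, the primary outcome is DR confirmed by dilated examination at the hospital. Under Strategies of analysis (and again in the Statistical Plan at the end of the document), the primary ITT population is everyone offered a hospital referral, whether or not they go. In UR that is every patient. In TR it is only those whose images suggest a need for further investigation or are inadequate. The Hypothesis is about identifying proportionately more diabetic patients with DR.

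**The concern.** The UR planning rate lies above every prevalence figure the protocol prints, before any allowance for non-attendance. Low attendance after referral is also the reason given for doing the trial, so a UR yield that needs nearly everyone to attend sits badly with the Rationale.

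The two planning rates also describe different groups: unselected diabetic patients in UR, and patients pre-selected for likely DR in TR. Part of the 20-point gap would appear through selection alone, even if telemedicine found no more DR among the patients enrolled.

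At stake is what the 90% power means. If it does not apply to the question in the Hypothesis, a null result on that question could be read as evidence of no difference when the trial had little chance of showing one.

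**Working it through.** **1. The plan's own figure.** Inputs from Sample size estimates: 30% vs 50%, two-sided 0.01, 90% power, design effect 2. Pooled-variance formula:

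n per arm = [z(α)·√(2·p̄·q̄) + z(β)·√(p₁q₁ + p₂q₂)]² / (p₁ − p₂)², with p̄ = 0.40.

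- Two-sided 0.01: (2.576·√0.48 + 1.282·√0.46)² / 0.04 = 2.654² / 0.04 = 176.1, so 177. Times design effect 2 and 2 arms: **708**.
- One-sided 0.01: (2.326·√0.48 + 1.282·√0.46)² / 0.04 = 153.9, so 154. Times 4: **616**, the stated figure.
- Other two-sided formulas give 688 (unpooled), 704 (arcsine) and 744 (continuity correction).
- Power of 616 at two-sided 0.01, with effective n = 308/2 = 154 per arm: (0.20·√154 − 2.576·√0.48)/√0.46 = 1.03, which is **84.8%**. The planned 640-800 patients give 86.4-93.8%.

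**2. The UR rate.** UR rate = prevalence × attendance. The documents give no attendance figure, so 10-50% below is an assumption.

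| Prevalence | 10% attend | 50% attend | 100% attend | Attendance needed for 30% |
|---|---|---|---|---|
| 12% | 1.2% | 6.0% | 12% | 250% |
| 18% | 1.8% | 9.0% | 18% | 167% |
| 30% | 3.0% | 15% | 30% | 100% |
| 35% | 3.5% | 17.5% | 35% | 86% |
| 40% | 4.0% | 20% | 40% | 75% |

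The last three prevalences are not in the documents. They show what the 30% would require.

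**3. Ceiling on the difference per enrolled patient.** TR yield cannot exceed prevalence and UR yield cannot be below zero, so the difference cannot exceed prevalence. At 12-18% a 20-point difference is out of reach at any attendance.

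**4. Power with TR held at 50% of image-selected referrals** (308 per arm, design effect 2, two-sided 0.01): UR 18% gives 99.98%, and UR 12% or lower gives nearly 100%. If the planned risk ratio of 5/3 is kept instead, 18% vs 30% gives 45.6% and 12% vs 20% gives 25.3%.

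**5. Power per enrolled patient.** Assumed: prevalence 18%, UR attendance 30%, image sensitivity 85%, TR attendance after a positive image 60%, 308 enrolled per arm, design effect 2.

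- UR = 0.18 × 0.30 = 5.4%. TR = 0.18 × 0.85 × 0.60 = 9.2%.
- SE = √[2 × (0.054 × 0.946 + 0.0918 × 0.9082)/308] = 0.0295. Difference/SE = 0.0378/0.0295 = 1.28.
- Power by the normal formula: about **10%** at two-sided 0.01 and **25%** at 0.05, the level that matches the 95% CI to be reported. With 6 df (8 centres minus 2 arms): about 5% and 19%.
- Higher prevalence with the other inputs unchanged, at 0.01: 30% gives 9.0% vs 15.3% and about 19% power; 40% gives 12.0% vs 20.4% and about 29%.

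**The case against.** Three points can be made for the plan.

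First, a reader might infer that 30% is impossible. The documents do not support that. The 12-18% describes diabetic populations in general. The trial enrols people aged 50 or over at urban and peri-urban diabetes centres, the kind of patients in whom the protocol says DR is commoner, and no upper figure is given. The low attendance describes conventional referral. UR patients here are counselled, and those who live beyond 25 km or have difficulty travelling are excluded. This stands, but an unquantified increase is not support for 30%.

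Second, a reader might infer that the trial as planned is underpowered. That does not follow for the written primary analysis, which counts those offered referral. Take the inputs of step 5 and an assumed image specificity of 70-95%, ignoring ungradable images. The TR rate per referral is then 0.0918/(0.153 + 0.82 × 0.30) = 23% up to 0.0918/(0.153 + 0.82 × 0.05) = 47%, against 5.4%. Power at two-sided 0.01 is about 97% to nearly 100% by the normal formula. This stands too. It is power for a contrast created partly by image selection, not for finding more DR among the patients enrolled.

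Third, the recruitment target counts patients eligible for referral, so TR might enrol many more than 308. With the referred fractions above (39.9% and 19.4%), 308 referrals would need 308/0.399 = 772 to 308/0.194 = 1,588 enrolled. Keeping UR at 308 and the design effect at 2, SE = √[2 × (0.0511/308 + 0.0834/772)] = 0.0234, or 0.0209 with 1,588. Power at 0.01 is then about 17% to 22%, which is still low.

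**Conclusion.** The point holds in a limited form. Assumption (i) is unsourced and exceeds every prevalence figure in the protocol even at full attendance. Reaching 30% would take a clinic prevalence of at least 30% with everyone attending, or a still higher prevalence with somewhat fewer (40% with 75%). That is not excluded, but nothing in the protocol supports it and the Rationale points the other way. Assumption (ii) is on a different, image-selected denominator, so the planned difference does not measure what the Hypothesis describes.

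The 90% power is therefore not tied to rates the protocol supports. The direction of the error is not fixed: nearly 100% power on the per-referral comparison with TR at 50%, and about 10% (two-sided 0.01) or 25% (0.05) per enrolled patient in the worked example. The example rests on assumed attendance and sensitivity and illustrates the scale; it is not a forecast.

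The arithmetic error does not depend on any of this: the stated inputs need about 708 patients, and 616 gives about 85% power. The planned 640-800 spans 708, so recruitment could cover this shortfall.

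**What to change.** 1. Replace assumptions (i) and (ii) with rates per enrolled patient, built from stated and sourced components: UR = prevalence × attendance; TR = prevalence × image sensitivity × attendance after a positive image, plus a term for patients referred with inadequate images. Give the prevalence expected in clinic patients aged 50 or over, with a range.
2. Align the primary ITT population under Strategies of analysis, in both places where it appears, with that denominator: all enrolled patients in each arm. Without this, the sample size and the primary analysis would disagree.
3. State how many patients will be enrolled in each arm, as distinct from found eligible for referral. Restate the power, or the smallest detectable risk ratio, for that number in 8 centres.
4. Correct the sample size statement: either about 708 at two-sided 0.01, or 616 with about 85% power.

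Cost: changes to the protocol text, and a record in the database of every enrolled TR patient, including those not referred. The correction itself needs no extra patients. The restated power may be much less favourable on the per-enrolled scale, and it should be reported even so.

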### *Statistical analysis*

The data will be analysed using Stata14 (StataCorp Texas). All analyses will take account of the cluster trial design, i.e. the clinic/centre is the unit of randomization. The survey suite of commands ("svy") in Stata will be used for all regression models and cross tabulations.

We will first compare the distribution of characteristics between the trial arms including important prognostic covariates such as age, sex, duration of diabetes. The primary outcome will be analysed using Poisson regression comparing the proportion of DR in the TR arm with that in UR and report the risk ratio (RR) and 95% Confidence Interval (CI) in unadjusted analysis and covariate adjusted analysis. These analyses will be undertaken for the ITT and PP populations. The ITT primary outcome analysis will represent the trial main result.

For the secondary outcome we will investigate characteristics associated with hospital attendance using Poisson regression in a model including randomised arm. We will first check whether characteristics of attendance vary by randomised arm in separate analyses before combining in a single model.

We will also report descriptive analyses based on the semi structured interviews. These will be transcribed into a data base and text analysis techniques will be used to group the responses (this may necessitate translation into English if Tamil software is not available).

**Ethical consideration:** The protocol including the procedures for fully informed consent will be presented for approval from the Research Committee and the Institutional Review Board of Aravind Eye Hospital, India. Eligible participants in the telemedicine arm will be given an information sheet in the local language which will explain the purpose of the study and what

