#### *Statistical analysis*

The data will be analysed using Stata14 (StataCorp Texas). All analyses will take account of the cluster trial design, i.e. the clinic/centre is the unit of randomization. The survey suite of commands ("svy") in Stata will be used for all regression models and cross tabulations.

We will first compare the distribution of characteristics between the trial arms including important prognostic covariates such as age, sex, duration of diabetes. The primary outcome will be analysed using Poisson regression comparing the proportion of DR in the TR arm with that in UR and report the risk ratio (RR) and 95% Confidence Interval (CI) in unadjusted analysis and covariate adjusted analysis. These analyses will be undertaken for the ITT and PP populations. The ITT primary outcome analysis will represent the trial main result.

For the secondary outcome we will investigate characteristics associated with hospital attendance using Poisson regression in a model including randomised arm. We will first check whether characteristics of attendance vary by randomised arm in separate analyses before combining in a single model.

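### The stated two-sided alpha of 0.01 matches neither the sample size of 616 nor the 95% interval planned for the main result, and no test level is named in the analysis sections

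*Protocol*

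**What the plan says.** The Protocol, under Sample size estimates, lists its assumptions: "The proportion of patients in UR diagnosed with DR at AEH is 30% of the referred patients"; "The proportion of patients in TR diagnosed with DR at AEH is 50% of the referred patients"; "Power of 90% and alpha of 0.01 for a 2 sided test"; and a design effect of 2. It concludes: "The estimated total sample size is 616 patients, equally distributed in each arm". It then plans for more than this minimum: "Each of the 8 centres will recruit between 80 and 100 patients eligible for referral to AEH".

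Under Statistical analysis, the primary outcome is compared between arms by Poisson regression, and the plan is to "report the risk ratio (RR) and 95% Confidence Interval (CI) in unadjusted analysis and covariate adjusted analysis". The same section says: "The ITT primary outcome analysis will represent the trial main result". The Statistical Plan at the end of the document repeats this text. Neither copy states a significance level for the primary test, refers back to 0.01, or explains why the sizing level and the interval level differ.

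**The concern.** Two things in the text do not fit together.

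First, the only alpha in the document is 0.01, while the only inferential output described for the main result is a 95% interval, which corresponds to a two-sided 5% test. A primary p-value between 0.01 and 0.05 would give an interval that excludes 1 and yet miss the alpha used for sizing. The document does not say how such a result is to be read.

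Second, the sample size line does not follow from its own assumptions. If 616 does not give 90% power at two-sided 0.01, then the alpha, the sidedness, the power or the number of patients is misstated. The design claim for the headline comparison is then wrong as printed.

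At stake are the error rate that readers attach to the main result and the power that the protocol says it has.

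**Working it through.** **Inputs (Protocol, Sample size estimates).** p1 = 0.30 (UR), p2 = 0.50 (TR), difference 0.20, power 90%, two-sided alpha 0.01, design effect 2, total 616 in two equal arms.

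**Formula.** Comparison of two proportions, normal approximation, pooled variance under the null:

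n per arm = [z(alpha) × √(2 × 0.40 × 0.60) + z(power) × √(0.30 × 0.70 + 0.50 × 0.50)]² / 0.20²

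The square roots are √0.48 = 0.6928 and √0.46 = 0.6782. The total is n rounded up, × 2 arms × design effect 2.

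**Trying to reproduce 616 (90% power, z = 1.2816).**

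| Level | z(alpha) | n per arm before design effect | Total |
|---|---|---|---|
| two-sided 0.01 (as stated) | 2.5758 | (1.7846 + 0.8692)² / 0.04 = 176.1, so 177 | 708 |
| one-sided 0.01 = two-sided 0.02 | 2.3263 | (1.6117 + 0.8692)² / 0.04 = 153.9, so 154 | 616 |
| two-sided 0.05 | 1.9600 | (1.3579 + 0.8692)² / 0.04 = 124.0, so 124 | 496 |

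The stated inputs give 708. Other common variants at two-sided 0.01 do not rescue 616: unpooled variance gives 688 and a continuity correction gives 744. The one-sided 0.01 calculation gives 616 exactly. Two-sided 0.05 with 95% power comes close, at 612, but contradicts both the stated alpha and the stated power.

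**Power that 616 gives.** Effective number per arm: 616 / 2 arms / 2 = 154. Power = Φ[(0.20 × √154 − z(alpha) × 0.6928) / 0.6782], with 0.20 × √154 = 2.4819.

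- Two-sided 0.01: Φ[(2.4819 − 1.7846) / 0.6782] = Φ(1.028) = 84.8%.
- Two-sided 0.05: Φ[(2.4819 − 1.3579) / 0.6782] = Φ(1.657) = 95.1%.

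The gap, 95.1 − 84.8 = 10.3 percentage points, is the chance under the protocol's own alternative that the primary p-value falls between 0.01 and 0.05.

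**Power at the planned recruitment.** 8 × 80 = 640 and 8 × 100 = 800, that is 160 and 200 effective per arm with the design effect held at 2.

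- 640 at two-sided 0.01: Φ[(2.5298 − 1.7846) / 0.6782] = Φ(1.099) = 86.4%.
- 800 at two-sided 0.01: Φ[(2.8284 − 1.7846) / 0.6782] = Φ(1.539) = 93.8%.

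The 708 needed is 88.5 per centre, inside the planned 80 to 100. Holding the design effect at 2 is favourable at the upper end, because larger centres raise it if the within-centre correlation is fixed.

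**What the intervals would look like.** If exactly 30% and 50% were observed at 616, RR = 0.50 / 0.30 = 1.67. The standard error of log RR is √[0.70 / (0.30 × 154) + 0.50 / (0.50 × 154)] = 0.147. The 95% interval is about 1.25 to 2.22 and the 99% interval about 1.14 to 2.43. On this approximation both exclude 1, so the choice of level matters for results weaker than the design effect size.

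**The case against.** The strongest reply is that a 95% interval is a usual reporting format and sets no test level. The analysis sections nowhere say that an interval excluding 1 makes the trial positive. The one alpha in the document is 0.01, and testing at 0.01 while displaying a 95% interval is coherent. This stands. A reader might infer that the trial's false-positive rate is five times the planned one; that holds only if the interval is the decision rule, which the text does not say. Nor does the text support a suggestion that the level would be picked after seeing the p-value.

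The reply also notes that sizing at a stricter level than the interval costs no power: at two-sided 5%, 616 gives 95.1% against the 90% planned. This is correct under the normal approximation. The mismatch does not make the analysis biased, invalid or underpowered at the conventional level.

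A reader might also infer that power at two-sided 0.01 is only about 54%. That figure comes from a t reference with 6 degrees of freedom (86% at two-sided 0.05). The protocol names no degrees of freedom, and the drop is due to having eight centres. It is a separate matter from the alpha and the interval.

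Two things are not answered. The analysis sections give no other criterion for the main result, so the reading of a p-value between 0.01 and 0.05 is left open. And the reply cannot explain 616, which is wrong for the stated alpha, sidedness and power whatever role the interval plays. A separate analysis plan could name the test level, but it would not correct the figure printed in the protocol.

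**Conclusion.** The point holds as an inconsistency to be corrected, not as a flaw that invalidates the trial. Three two-sided levels are in play: 1% as stated, 2% as implied by 616, and 5% as the complement of the reported interval. It would be too strong to say that the trial is sized for a two-sided 1% test; that is true only of the label. At that level 616 gives about 85% power, some 5 points below the stated 90%, and 90% power needs 708, which is 92 more patients. Recruitment of 640 to 800 would bring power to about 86% to 94%, so the shortfall may close in practice.

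That 616 came from a one-sided calculation is an inference from the exact match; the document does not say how it was derived. All figures take the 30% and 50% rates and the design effect of 2 as given and use the normal approximation.

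**What to change.** Before outcome data are seen, state one two-sided level for the primary test and use it in Sample size estimates and in both copies of the Statistical analysis text. Either option is consistent:

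- Restate alpha as two-sided 0.05, keep the 95% interval, and give the power as about 95% at 616.
- Keep two-sided 0.01, base the conclusion on a 99% interval, and give the power as about 85% at 616. Restating the target as 708 for 90% power is also possible and lies within the recruitment already planned.

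In both cases, add that these are normal-approximation figures and that power will be lower if the analysis uses a t reference with few degrees of freedom from eight centres.

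The cost is about one line of text. The second option also means a less favourable stated power if 616 is kept. Neither option changes the randomisation or the data collected.

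### The sample size of 616 does not follow from the stated inputs, which give 708; at two-sided 1%, 616 gives about 85% power, not 90%

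*Protocol*

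**What the plan says.** All the inputs stand together in the Protocol, under sample size estimates:

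- Universal referral arm: "The proportion of patients in UR diagnosed with DR at AEH is 30% of the referred patients".
- Telemedicine arm: "The proportion of patients in TR diagnosed with DR at AEH is 50% of the referred patients".
- Error rates: "Power of 90% and alpha of 0.01 for a 2 sided test".
- Clustering: a design effect of 2, attributed to a cited population study.

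The result is then given: "The estimated total sample size is 616 patients, equally distributed in each arm". The next sentence sets recruitment: "Each of the 8 centres will recruit between 80 and 100 patients eligible for referral to AEH". No dropout allowance, formula or software is given for the calculation.

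Elsewhere, the procedures under the study plan say that eight centres are randomised, four to each arm. The statistical analysis section says the primary outcome will be reported as a risk ratio with a 95% confidence interval. It sets no 1% threshold.

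**The concern.** Every input needed to reproduce the total is on the page, and the total does not come out. A reader who takes the paragraph at its word would believe that 616 patients give a 10% chance of missing a true difference of 30% against 50% when judged at two-sided 1%. On the same inputs that chance is about 15%. The calculation justifies the size of the trial, so it should be reproducible. A team that relies on 616 as the requirement has no reason to aim for the upper part of its own recruitment range.

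**Working it through.** **Inputs** (all from the sample size section): p1 = 0.30, p2 = 0.50, difference 0.20, mean proportion 0.40, power 90% (z = 1.2816), design effect 2, equal arms, no dropout allowance.

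**Formula** (pooled variance under the null, unpooled under the alternative), per arm before clustering:

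n = [z_alpha × sqrt(2 × 0.4 × 0.6) + z_power × sqrt(0.3 × 0.7 + 0.5 × 0.5)]² / 0.2²

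The two square roots are 0.6928 and 0.6782.

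**Reproducing 616.** Total 616 is 308 per arm, or 308 / 2 = 154 per arm before the design effect. With a one-sided 1% critical value (2.3263, the same as two-sided 2%):

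n = (1.6117 + 0.8692)² / 0.04 = 6.155 / 0.04 = 153.88, rounded up to 154; 154 × 2 × 2 = **616**.

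**The inputs as stated.** With a two-sided 1% critical value (2.5758):

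n = (1.7846 + 0.8692)² / 0.04 = 7.0425 / 0.04 = 176.06, rounded up to 177; 177 × 2 × 2 = **708**.

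The gap is 708 − 616 = 92 patients, or 92 / 708 = 13% of the requirement.

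**Is it the choice of formula?** Totals at two-sided 1%, 90% power and design effect 2:

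| Method | Total |
|---|---|
| Unpooled variance | 688 |
| Arcsine | 704 |
| Formula above | 708 |
| Pooled variance in both terms | 716 |
| Log odds ratio | 728 |
| Continuity-corrected | 744 |
| Log risk ratio | 764 |

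The smallest is 72 above 616. To reach 616 from 177 per arm, the design effect would have to be 616 / (2 × 177) = 1.74.

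**Other routes to about 616.** Two-sided 1% with 85% power gives 155 per arm and 620. Two-sided 5% with 95% power gives 153 per arm and 612. Neither is exact, and neither matches the stated inputs. Two-sided 5% with 90% power gives 496.

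**Power of 616 at two-sided 1%.**

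Phi[(sqrt(154) × 0.2 − 2.5758 × 0.6928) / 0.6782] = Phi[(2.4819 − 1.7846) / 0.6782] = Phi(1.028) = **84.8%**

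It is 86.1% with unpooled variance and 81.8% with continuity correction.

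**Power over the planned range** (8 × 80 = 640 to 8 × 100 = 800), same formula, effective number per arm = total / 4:

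| Total | Effective per arm | Two-sided 1% | Two-sided 5% |
|---|---|---|---|
| 616 | 154 | 84.8% | 95.1% |
| 640 | 160 | 86.4% | 95.8% |
| 720 | 180 | 90.7% | 97.5% |
| 800 | 200 | 93.8% | 98.5% |

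At two-sided 1%, 90% is reached at about 704 to 708 patients: 704 / 8 = 88 and 708 / 8 = 88.5 per centre.

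**Two limits on these figures.**

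- *Few centres.* Normal quantiles ignore that only eight centres are randomised. Assume a t reference with 8 − 2 = 6 degrees of freedom. The two-sided 1% critical value rises from 2.576 to 3.707. With noncentrality 0.2 / sqrt(0.46 / 154) = 3.66, 616 patients give about 54% power at 1% and about 86% at 5%.
- *Fixed design effect.* Assume that a design effect of 2 belongs to 616 / 8 = 77 per centre. The implied intracluster correlation is 1 / 76. At 88.5 per centre the design effect becomes 1 + 87.5 / 76 = 2.15, and 708 patients give about 87.5% power. The Protocol does not say which centre size its value of 2 refers to.

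**The case against.** The best defence is that 616 is not the recruitment target. The very next sentence plans 640 to 800 patients, and the midpoint, 720, gives 90.7% power at two-sided 1%. This largely stands: the number actually needed lies inside the plan. It does not rescue the stated total, because the range is not presented as a correction or contingency, and its lower part stays below 90%, by up to about 4 points.

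A second defence is that the analysis section reports a 95% confidence interval and applies no 1% rule. Read at two-sided 5%, 616 gives about 95% power. This also stands as a limit on the harm. A reader might infer that the trial runs a 15% risk of missing its planned effect; that holds only if significance is judged at 1% and recruitment stops at 616. It still does not make the paragraph right, since the 90% is claimed at 1% two-sided.

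A reader might also infer that the trial was sized on a one-sided test. The exact match at 154 per arm is strong evidence of a one-sided critical value, but the Protocol names no formula or software, and other departures land within 4 patients of 616. The cause remains an inference, and the finding does not depend on it.

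**Conclusion.** The point holds as an error of statement: 616 is not the answer to the calculation described. On the stated inputs the total is 708 (688 to 764 across standard methods), and 616 gives about 85% power at two-sided 1%. It should be fixed, but it does not by itself undermine the trial. Only recruitment below about 88 to 89 per centre falls short of 90%.

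The documents do not support the stronger conclusion that the planned trial is too small because of this slip. All the main figures take the design effect of 2 as fixed and use a normal approximation. With eight randomised centres true power is lower than any of them, so neither 85% nor 708 should be read as a full assessment of power.

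**What to change.** In the Protocol's sample size section, do one of two things:

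- keep 616 and restate power as about 85% at two-sided 1%; or
- give 708 (about 89 per centre) as the number for 90% power.

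With either, add a sentence saying that the figure holds the design effect at 2 and rests on a normal approximation with no allowance for only eight centres, so true power is lower.

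The cost is one or two sentences of text. The second option needs no new centres and no wider recruitment range, since about 89 per centre already lies between 80 and 100. The Protocol repeats neither the total nor the power elsewhere, so nothing else has to change with it.
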